**Discussion:**

This study will provide evidence regarding the effectiveness of a multi-faceted intervention for reducing non-medically indicated caesareans in a low-income country. By combining qualitative and quantitative methods, the study’s findings will allow understanding the factors that could influence the intervention process and ultimately the intended outcomes.

**Trial registration:**

The DECIDE trial is registered on the Current Controlled Trials website under the number ISRCTN48510263 on January 28, 2014.

**Electronic supplementary material:**

The online version of this article (doi:10.1186/s12884-016-1112-8) contains supplementary material, which is available to authorized users.

## Background

In Burkina Faso, although the national caesarean rate increased from 0.7 % in 2003 [1] to 2 % in 2010 [2], it remains well below the minimum rate of 3 % required to meet the needs [3]. The institutional caesarean rate has risen steadily since the introduction of a policy to subsidize emergency obstetric care in 2006, which significantly increased access to caesareans [4]. Under this policy, caesarean costs are subsidized up to 80 % (100 % in some districts) and transportation is fully funded between primary health centres and referral hospitals, where caesareans are performed. Similar policies have led to very high institutional caesarean rates in other sub-Saharan countries [5]. In fact, according to Burkina Faso’s Ministry of Health, the rate surpassed 40 % in some hospitals in 2013 [6]. Research has shown, however, that between 12 and 24 % of caesareans in that country are not medically indicated [7, 8].

In Burkina Faso, as in many African countries, excessive caesarean rates in some hospitals have been attributed to limited training and knowledge of personnel [7, 9]. In those facilities, it is not only obstetricians who assess indications for caesareans, but also general practitioners and nurses trained in emergency surgery (a 6-month training program involving 1 month of theoretical courses and a 5-month practicum in surgical and obstetric emergencies).

While greater access to caesareans is a necessity in countries where the national rate is below 10 % [10], it is imperative that quality improvement programs be implemented at the same time to prevent excessive and inappropriate increases in caesarean rates [11]. High rates of non-medically indicated caesareans (NMIC) are associated not only with adverse health outcomes for mothers and infants, but also with high public spending on health, presenting equity and efficiency challenges for low-resource countries [12–19].

Various strategies for reducing the proportion of NMICs have been tested and evaluated: 1) obtaining a second opinion on the indication for a caesarean before proceeding [20]; 2) encouraging normal, midwife-assisted deliveries outside the hospital [21, 22]; 3) establishing guidelines based on recommendations of professional associations [23, 24]; and 4) auditing indications for caesareans and providing feedback to health professionals, combined with instituting best practices for managing labour and performing caesareans [25]. A meta-analysis of 10 randomized controlled trials in high-income countries showed a 19 % reduction in caesarean rates using one or a combination of the different approaches cited above. The most effective strategies were clinical audits with feedback (RR = 0.87; 95 % CI = 0.81, 0.93), continuous quality improvement strategies (RR = 0.74; 95 % CI = 0.70, 0.77), and multi-faceted interventions combining several approaches (RR = 0.73; 95 % CI = 0.68, 0.79) [26, 27].

Furthermore, the use of SMS (Short Message Service) technology appears to have a positive, and less costly, impact on the continuing education of healthcare providers in sub-Saharan Africa [28–30]. Indeed, studies on its use have shown SMS is easy to implement and produces positive results in terms of improved knowledge and practices among health professionals in different contexts [31–33].

While the results of randomized controlled trials in high-income countries are encouraging [25], we found no evidence that these interventions, whether alone or in combination, are effective in reducing NMIC rates in low- or middle-income countries.

The objective of the DECIDE (Appropriate decision for caesarean section in Burkina Faso) trial is to evaluate the effectiveness and understand the implementation of an intervention combining three potentially effective approaches for reducing NMIC rates: 1) training in best practices during labour and delivery to favor vaginal delivery for low-risk women; 2) clinical audits based on objective criteria for the main indications for caesareans; and 3) SMS-based reminders to support decisions regarding clinically indicated caesareans.

### Hypotheses

Our main hypothesis is that clinical audits in healthcare facilities, combined with training and decision-support reminders to health professionals, will help reduce the NMIC rate by at least 50 %.

Our secondary hypotheses are that the intervention will improve: 1) health professionals’ knowledge; 2) the quality of caesareans; and 3) maternal and perinatal outcomes.

Regarding implementation, we posit that health workers will both appropriate and appreciate all three components of the intervention, and that any heterogeneity in results will be explained by the specific contexts of the different hospitals [34, 35].

## Methods

### Study design

This is a multicentre cluster randomized controlled trial of a complex intervention combined with an implementation analysis. To understand the reasons underlying the intervention’s effectiveness (or lack thereof), the heterogeneity of its effects, and role of context, it is essential that effectiveness and implementation (including fidelity) be analyzed together [36, 37]. This is a fundamental approach in operational research in the health field [38, 39]. To avoid contamination bias between clinicians in the same service, the unit of randomization and intervention is the hospital.

### Inclusion and exclusion criteria

A hospital was eligible for the trial if it had a functional operating room and had performed at least 200 caesareans in 2012. Twenty-two public hospitals were included in the trial between May and June 2014, out of a total of 24 eligible hospitals (91.6 %). Two university hospitals were excluded due to the high number of personnel in training. The 22 hospitals in the trial are representative of Burkina Faso’s current health system, spanning the full range in terms of context (urban versus rural), level of care (district and regional hospitals) and qualifications of health personnel. This process thus guaranteed a certain external validity of the results.

The intervention directly targets health professionals who provide obstetric care in the participating hospitals, while indirectly targeting the women giving birth there. The health professionals have been trained in the management of labour and delivery, with some also trained to perform caesareans. All health professionals involved in managing deliveries in their institutions were included in the study (*n* = 978). This total consisted of obstetricians and gynaecologists (*n* = 39), general practitioners (*n* = 32), physician anaesthetists (*n* = 3), nurses (*n* = 463), and midwives (*n* = 441). Maternity services personnel who were not involved in obstetric care in the labour room were excluded from the trial (*n* = 446).

The first 100 women with caesarean deliveries in the 22 hospitals during a 6-month period in the year preceding the intervention (May 2 to November 2, 2014) were included in the study. The first 100 women with caesarean deliveries in the 6 months following the end of the intervention will also be included. As the intervention will last 1 year, the pre- and post-intervention data collection periods will cover the same months of the year to avoid any seasonality bias. Women whose caesareans were performed in another hospital and who were subsequently transferred to a participating hospital will be excluded from the study.

### Activities in the intervention group

The activities will be conducted from May 2015 to April 2016. The sequence of activities over the 12 months will be directly focused on developing local leadership and strengthening the obstetric teams’ capacities. To achieve this goal, the intervention will be implemented in several stages. Figure 1 shows the logic of the intervention [40–42].

**Fig. 1 Fig1:**
[figure not shown]
show the logic of the intervention

The intervention will begin with the training of local trainers on: 1) evidence-based standards for the management of labour, the reasoning used to diagnose the main indications for caesareans, and the quality of the surgical procedure; and 2) conducting clinical audits of indications for caesareans based on objective criteria (criteria-based clinical audits, CBCA). The trainers will create CBCA teams in their own hospitals and will organize training for obstetric teams on best practices. With a view to sustainability, no financial incentive will be given to local trainers or to health professionals who undergo the training in the intervention hospitals. Thereafter, decision-support reminders of evidence-based criteria for diagnosing the main indications for caesareans, conveyed via SMS, will be used to supplement the staff training.

The intervention consists of five stages:
*Training the trainers:* The local trainers are the chiefs of maternity services in the intervention hospitals (one physician per hospital). In May 2015, the trainers attended a 3-day training session led by two experts from the Society of Gynaecologists and Obstetricians of Burkina (SOGOB). The training was based on the WHO guidelines for managing complications of pregnancy and childbirth [43] and clinical decision algorithms that had been developed as part of this study (see Additional files 1, 2, 3, 4, 5 and 6). The session included 2 days of training on: 1) the diagnostic reasoning involved in identifying the main indications for caesareans (previous caesarean, prolonged/obstructed labour, pre-eclampsia/eclampsia, foetal distress); 2) the quality of the surgical procedure; and 3) the decision algorithms validated by the experts. A third day was allocated to training on conducting CBCAs.
*Establishing and training a multidisciplinary audit committee in each intervention hospital:* Setting up these CBCA committees (consisting of physicians, midwives, nurses, and administrators) will involve: a) identifying and training people who will be responsible for collecting data on caesareans; and b) training committee members on how to conduct CBCAs.
*Setting up the audit cycle:* In each intervention hospital, the audit committee will implement CBCAs according to the approach proposed by WHO [44]. Monthly audit meetings are recommended to analyze the caesareans performed in the health facility. A caesarean audit guide prepared as part of this study (see Additional file 7) will be distributed to each audit committee member. It describes the steps involved in conducting an audit, from preparation all the way to closing the session, offers proposals regarding the roles of the different actors involved in the process, and suggests various media and data sheets needed to conduct audits.
*Training of maternity teams on best practices:* The local trainers will train the maternity teams in each hospital. First they will assess the needs for training in best practices. Then they will organize four training sessions on best practices (one session for each of the four main indications) during the intervention period. The trainers will select the topics based on areas in need of improvement, as identified in the audit meetings. As such, the content will be tailored to local contexts and situations.
*Decision-support reminders:* Health professionals will receive weekly decision-support reminders regarding diagnostic reasoning and the relevance of indications for caesareans. This strategy will be applied from the moment best practices training begins and audits are conducted, all the way to the end of the intervention period. The reminders will be sent on workdays, in the afternoons, via SMS messages. Once a week, each health professional will receive a clinical recommendation (see Additional file 8) on the diagnostic reasoning regarding the selected caesarean indications (previous caesarean, prolonged/obstructed labour, pre-eclampsia, eclampsia, foetal distress). Diagnostic reasoning criteria were established from the reference documents that were used for training and validated by expert consensus.

### Control group

No intervention is planned for the control group as part of this project.

### Implementation analysis

The intervention has been carefully planned and is evidence-based, but to be effective it must be correctly implemented [45]. Thus, we will need not only to verify implementation fidelity but also to understand its process. To do this, we will use a two-pronged strategy.

The first component, *implementation monitoring,* will involve monitoring and facilitating implementation of the intervention’s different steps. Monitoring will be done via quarterly visits to each intervention hospital in which the following criteria will be assessed: a) training schedule respected and attendance list available; b) decision algorithms available; c) schedule of audit meetings respected and attendance list available; d) audit recommendations implemented; and e) decision-support SMS message system functional.

We will inventory all training provided to staff in the maternity services of the hospitals being monitored (topics, content, number of participants and their profiles, duration, organizer). This information will be recorded on a training census form in collaboration with the chiefs of maternity services. We will also document any movement of personnel from the intervention group to the control group.

The *qualitative component* will consist of four stages (see additional file 9):Analysis of the pre-intervention situationThis analysis is focused on NMIC rates and their inter-hospital variability. In the train-the-trainers workshop, information on overall NMIC rates and their variability among hospitals (anonymized) was presented to solicit the perceptions of the group as a whole (*n* = 1, 11 participants) and then of each participant in individual interviews (*n* = 11).
Analysis of the implementation of the interventionFor this, 3 months after the train-the-trainers workshop at the start of the intervention, the analysis of the overall findings of the study on caesareans and on variations in NMIC rates will be repeated using data collected from groups and individuals (*n* = 22), i.e., two persons per hospital who decide on caesareans and did not attend the first workshop. Then, in months 6 and 12 of the intervention and in each hospital (*n* = 11), we will conduct group discussions, as well as non-participant observation of an audit committee meeting and interviews with two health professionals who decide on caesareans (*n* = 22). The health professionals’ views on the relevance and effectiveness of the intervention strategies will be collected, as well as their opinions regarding the various factors that could influence, either positively or negatively, the intervention process and ultimately the intended outcomes.
Analysis of events in the control groupFor this analysis, group discussions with the maternity teams of each control hospital are planned for the 12th month of the intervention. These discussions will focus on NMIC rates and their variability among the hospitals. A summary will also be prepared of any significant events that have occurred in the maternity service over the intervention period, especially any training provided to health professionals. The aim is to take into account any event that might influence the key indicator of the intervention’s impact.
Analysis of the potential for transferring the intervention outcomes to other contextsIndividual interviews will be conducted with key stakeholders (health professionals, trainers, and the principal investigator) using an analytical framework developed specifically for this purpose [46].

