### Assessment criteria

These criteria were measured for a 6-month period (May 2–November 2, 2014) preceding the intervention year and will be measured again in the 6 months following the end of the intervention, corresponding to the same months of the year.

The primary assessment criterion is the NMIC rate.

We conducted a literature review to discern the diagnostic reasoning underlying evidence-based indications for caesareans. The four main indications for caesareans in Burkina Faso are: previous caesarean, prolonged/obstructed labour, pre-eclampsia, and acute foetal distress. In the 22 participating hospitals in the pre-intervention study, these four indications accounted for 76 % of all caesareans performed. The relevant references [47–70] were consulted and used to generate a provisional list of good practice criteria. Preference was given to evidence obtained through randomized controlled trials, considered the most rigorous. The provisional list of criteria was sent to 16 international and national experts (gynecologist-obstetricians, midwives, and a public health physician, see Additional file 10). The experts gave their opinions on the relevance of each criterion and proposed others. The criteria retained were those validated by at least two-thirds of the experts. We then developed clinical decision trees (algorithms) for managing the four main indications for caesareans and derived the criteria for NMIC.

The NMIC criteria are presented in Table 1. For each indication, all the criteria are considered simultaneously. A caesarean is judged to be non-medically indicated when all the criteria are met or when they are not documented and no opposing medical indication is provided. The NMIC rate was calculated for each hospital. This rate is the proportion of NMICs among all the caesareans performed for the four indications during the same period.

**Table 1 Tab1:** Criteria for non-medically indicated caesareans ^a^

Previous caesarean section	Prolonged/obstructed labour

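### Month-12 group discussions of NMIC rates in every control hospital fall immediately before the outcome window and are not recognised as an influence on it

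*Protocol article*

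**What the plan says.** Under Control group, the protocol article says: "No intervention is planned for the control group as part of this project". Under Implementation analysis, in the stage on events in the control group, it says that "group discussions with the maternity teams of each control hospital are planned for the 12th month of the intervention", and then: "These discussions will focus on NMIC rates and their variability among the hospitals". The same stage includes a summary of significant events, especially training. Its declared aim is to take account of anything that might influence the key indicator.

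The timing follows from three other sections. Activities in the intervention group: "The activities will be conducted from May 2015 to April 2016". Assessment criteria: the outcomes "will be measured again in the 6 months following the end of the intervention, corresponding to the same months of the year". Inclusion and exclusion criteria: "The first 100 women with caesarean deliveries in the 6 months following the end of the intervention will also be included".

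Potential limitations of the trial names four matters: a data-collection effect taken as similar in both arms, staff transfer from intervention to control hospitals, a plan to study control hospitals in depth, and the possible end of the subsidy. The in-depth study is offered as a way to understand the control arm. It is not presented as something that might itself alter the outcome.

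**The concern.** The control arm should show what happens to the NMIC rate without the intervention. A meeting about NMIC rates and how they differ between hospitals draws the attention of the maternity team to the primary outcome, days or weeks before its caesareans are counted. The Background lists "auditing indications for caesareans and providing feedback to health professionals" among the strategies for reducing NMIC, and a discussion of rates leans in that direction.

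There are two routes to a lower control rate. One is a change in decisions. The other needs no change in care: under Assessment criteria, a caesarean also counts as NMIC when the criteria are not documented and no opposing indication is given. A team prompted to think about NMIC may simply document more fully, and its measured rate then falls.

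Either route narrows the difference between arms in the very window used for the comparison. At stake are some power and a diluted effect estimate, from a contact that the trial itself creates and could avoid.

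**Working it through.** **Timing.** The intervention runs from May 2015 to April 2016, so month 12 is April 2016. The pre-intervention window was May 2 to November 2, 2014. The post-intervention window covers the same months, so it opens about May 2, 2016. There is no washout between the control discussions and the window. Because the first 100 caesareans per hospital are taken, the busier the hospital, the closer its sampled records lie to the meeting.

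**Contact by arm, as planned.**
- Control: group discussion in month 12, in all 11 hospitals, with NMIC rates and their variability as the stated focus.
- Intervention: group discussions in months 6 and 12 in all 11 hospitals, where the stated content is views on the strategies and on factors affecting implementation. Rates were presented to the trainers at the start, and the overall findings are revisited 3 months later. These teams also receive audits, training and weekly SMS.

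**The plan's own figure.** Sample size calculation gives two-sided α of 5%, power of 90%, ρ = 0.02, 100 caesareans per hospital, 22 hospitals and 2,200 records.
- Variance inflation factor (VIF) = 1 + (100 − 1) × 0.02 = 2.98, stated as 3. This reproduces.
- The section gives no control rate, so 2,200 cannot be checked from its own inputs. With an assumed 15% against 7.5%, the two-proportion formula gives 371 per arm, and 2 × 371 × 3 = 2,226, close to 2,200. The Background range of 12% to 24% gives 2,862 to 1,284.

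**Illustration of dilution.** Let p be the assumed baseline and r the assumed relative fall in the control rate caused by the discussion. Then p_c = p(1 − r), and the intervention rate is held at p_t = p/2. The effective n per arm is 1,100/3 = 366.7. Power = Φ[(d − 1.96·s0)/s1], where d = p_c − p_t, s0 = √[2·p̄(1 − p̄)/n], s1 = √[(p_c(1 − p_c) + p_t(1 − p_t))/n], and p̄ is the mean of p_c and p_t.

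At p = 15%:
- r = 0: d = 0.0750, s0 = 0.02334, s1 = 0.02317, z = 1.26, power 0.897, apparent risk ratio 0.50.
- r = 5%: p_c = 0.1425, d = 0.0675, s0 = 0.02299, s1 = 0.02286, z = 0.98, power 0.837, apparent risk ratio 0.53.
- r = 10%: p_c = 0.1350, d = 0.0600, s0 = 0.02264, s1 = 0.02253, z = 0.69, power 0.756, apparent risk ratio 0.56.

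Across the Background range, r = 10% takes power from 0.812 to 0.650 at p = 12%, and from 0.989 to 0.937 at p = 24%.

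**The case against.** The strongest reply is that the contact is not peculiar to the control arm. Intervention hospitals have group discussions in months 6 and 12 and individual interviews, so the month-12 meeting is partly parallel research contact. This stands as a limit on size. It does not remove the problem: for control teams it is the only NMIC discussion the protocol article plans, whereas intervention teams will already have had a year of audit, training and reminders.

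A reader might infer that control teams are told their own results and so receive the feedback being tested. The text does not support that. It names rates and their variability as the focus, but does not say that a team sees its own rate, cases or criteria. Where the article describes presenting rates, to the trainers, they were overall and anonymised. Caesarean data collection is described only for the 2014 and post-intervention windows, so any study rates available in month 12 would apparently be those of 2014. Details of the qualitative stages are in an additional file that is not shown. One discussion is also far from repeated criteria-based case audit with training sessions and weekly SMS.

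For the same reason, the risk ratio of 0.87 quoted in the Background for audit with feedback should not be used to size the effect. It comes from trials of such strategies in high-income countries, with caesarean rates as the outcome. It is neither an effect on NMIC nor the effect of one meeting.

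A reader might also conclude that a null result could not be interpreted. That goes too far. The likely bias is conservative and of unknown, possibly small, size.

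Finally, postponing the whole meeting would lengthen recall of events and leave only the intervention hospitals with contact before the window. The fix should therefore keep a month-12 contact in control hospitals.

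**Conclusion.** The point holds in a limited form. The article places a discussion of the primary outcome in all 11 control hospitals immediately before that outcome is sampled. This fits poorly with a control arm that is meant to receive no intervention, and the limitations section does not recognise it as an influence. The likely direction is towards no effect. That direction is a judgement: it assumes that the discussion affects teams with no earlier exposure more than teams already in the programme.

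The size cannot be derived from the documents. The fall in power from about 0.90 to 0.84 or 0.76 rests on an assumed 15% baseline, an assumed relative fall of 5% or 10% in the control rate, 1,100 records per arm, VIF 3, and no matching change in the intervention arm. It shows what is at stake and is not an estimate. The point merits a change because the exposure is avoidable at little cost.

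**What to change.** Limit the month-12 contact with control hospitals to the training census and the log of significant events, with no presentation or discussion of NMIC rates. Hold any discussion of rates in control hospitals after post-intervention data collection closes in November 2016. Recall of events is unaffected, because the event log stays in month 12. The cost is a later qualitative discussion in 11 hospitals, which may run slightly past the stated end date of November 2016.

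If the timing is kept, add this exposure to Potential limitations of the trial as a conservative contamination route, and say there what rate information the control teams were shown.
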